### Objectives

#### Primary objective

Our primary goal is to assess the acceptability and feasibility of a 12-week yoga vs. educational film program for RLS management in adults with moderate to severe RLS. Primary aims are as follows:Aim.1a. Assess participant recruitment and enrollment rates and determine optimal recruitment strategies. Reasons for refusal will be recorded and the information used to develop and implement strategies to address these barriers where appropriateAim.1b. Determine participant retention rates and adherence in the yoga and educational film groups, with 80% retention, 80% class attendance, 75% home practice (yoga group), and 80% completion of weekly logs serving as benchmarks for acceptability. Information on barriers to adherence will be collected and used to inform ongoing strategies to enhance compliance

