## Methods

### Participants

Forty-four ambulatory, overall healthy adults aged ≥ 18 years with confirmed moderate to severe RLS will be recruited and randomized to a 12-week beginner yoga program (*n* = 22) or a standardized 12-week educational film program (*N* = 22), modeled on interventions used in our previous trials [15, 87] (see Fig. 1).

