### Recruitment and study setting

Participants will be recruited from two sites: Morgantown, WV metropolitan area (WVU site) and Columbus, Ohio (The Ohio State University (OSU) site). In the WVU site, we will mail recruitment letters to all patients visiting a Morgantown area University Health Associates (UHA) clinic, who received a diagnosis of RLS (ICD-9 code: 333.94, 333.99) during the 5 years preceding study onset, as identified by electronic visit data. Consistent with Institutional Review Board (IRB) and Health Insurance Portability and Accountability Act (HIPAA) guidelines, the mailing list was obtained based on IRB approval of a waiver of research participants’ authorization for the use/disclosure of information. Only the minimum necessary information needed to identify potentially eligible subjects was accessed (i.e., name and mailing address). At both sites, we are recruiting from the community using local television, radio, and print media advertisements, as well as flyers and brochures posted in public places such as community bulletin boards (physical and electronic); health center waiting areas, and intranets. Study staff will also give presentations regarding the trial to interested lay and professional groups in the area, including clinician, support, university extension, and church groups, as well as other regional organizations and conferences. These strategies have proved effective in recruiting participants for previous studies of yoga-based interventions by WVU investigators in Morgantown, WV and by our partner investigators at OSU in Columbus, OH [52, 97–102].

Prospective study participants are being invited to contact the WVU study coordinator for further information. A member of the investigative team will describe the study, including eligibility criteria, to each potential participant over the telephone; those still interested will then be scheduled for a screening interview and baseline assessment, and sent a copy of the consent form to preview at their leisure prior to their first appointment.

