### Statistical methods

All analyses will be performed using SAS [145] or R [146]. For the primary feasibility aims, we will be evaluating recruitment and enrollment rates (all interested potential participants), acceptability of randomization (all enrolled subjects), retention, and adherence (all randomized participants). For the secondary aims, we will define the intent-to-treat (ITT) population as all subjects who are randomized with baseline assessments and at least one post-randomization assessment. The per-protocol analysis of the exploratory outcomes (RLS symptoms, sleep quality, mood, stress, and quality of life) will include all participants who completed both assessments and at least 75% of the classes.

*Feasibility of the proposed design* (*A.1*) will be evaluated in several ways:

*Recruitment*: we will examine recruitment time and success rates for different recruitment strategies and assess the percentage of interested volunteers who meet the study criteria, agree to participate and are randomized. We will use Fisher’s exact test to determine whether there are any differences in recruitment rates across the different strategies, and exponential regression model to assess the recruitment strategy on recruitment time.

*Retention*: will initially be assessed using descriptive statistics, including comparisons between retained individuals and drop-outs. The nonparametric Kaplan-Meier curve will be used to estimate the probability of retention over the duration of the study. If retention is unexpectedly low, we will use the proportional hazard model to assess retention differentials by treatment, demographic, and health-related factors to better target and retain specific groups in future trials.

*Randomization success*: (i.e., the two groups are similar demographically and on anthropometric and exploratory outcome measures at baseline) will be assessed using the one-sample run test. To evaluate *adherence* to the study protocol, we will determine missing-data rates at baseline and follow-up, class attendance (both groups), and completion of weekly logs.

*Treatment fidelity* (*A.2.1*) will be monitored and lapses recorded and compared between groups, along with outcomes of remediation strategies. We will use the Fisher’s exact (continuous data) and chi-square tests (using benchmark cut-offs) to determine potential differences in treatment adherence and fidelity.

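### Mailed letters are described only for WVU, yet the planned comparisons of recruitment strategies name no site term, so contrasts involving letters absorb any site difference in yield

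*Protocol article*

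**What the plan says.** Everything here is in the protocol article.

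- **Primary objective, Aim 1a:** "Assess participant recruitment and enrollment rates and determine optimal recruitment strategies". The strategy comparison therefore belongs to a primary aim.
- **Recruitment and study setting:** "Participants will be recruited from two sites", WVU and OSU. Letters are described for one of them: "In the WVU site, we will mail recruitment letters to all patients visiting a Morgantown area University Health Associates (UHA) clinic", limited to patients with an RLS diagnosis code in the preceding five years. Other channels are shared: "At both sites, we are recruiting from the community using local television, radio, and print media advertisements", together with flyers and brochures. Staff presentations are described without restriction to one site.
- **Statistical methods:** the population is given as "recruitment and enrollment rates (all interested potential participants". Success rates by strategy are first examined descriptively. Fisher's exact test is then used to "determine whether there are any differences in recruitment rates across the different strategies", and an "exponential regression model to assess the recruitment strategy on recruitment time" is planned. Site appears in neither analysis.
- **Interventions:** yoga classes have a studio at each site. The description of the film program gives the WVU Health Sciences Center as the place for each class and names no Columbus venue.

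**The concern.** One strategy exists at one site only. When letters are compared with the other strategies over all interested volunteers, every letter contact comes from WVU while the comparison group comes from WVU and OSU. Whatever makes yield differ between the sites is then credited to, or held against, the letters.

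The article itself gives a reason to expect such a difference. Success is counted as meeting the criteria, agreeing to take part and being randomized. As written, a Columbus volunteer must accept an even chance of allocation to weekly classes at WVU, and a Morgantown volunteer faces no such obstacle.

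At stake is the advice on recruitment that this pilot hands to the planned larger trial. Letters could look better or worse than they are, and effort could be directed accordingly.

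**Working it through.** **Inputs from the article.** Two sites; letters at WVU only; media, flyers and brochures at both; Fisher's exact test and an exponential regression with strategy as the only named factor; 44 participants randomized (Participants section), with no split by site. The article gives no yields, no numbers of interested volunteers and no counts by strategy or site. There is no planned figure to reproduce, and every rate below is an assumption.

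**Step 1: the bias.** Suppose strategy has no effect within a site. Let p_W and p_O be the yields at WVU and OSU, and w the share of community-strategy contacts that come from OSU.

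- Letters yield: p_W
- Community yield over both sites: (1 − w)·p_W + w·p_O
- Spurious difference: w·(p_W − p_O)

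This is zero if p_W = p_O. It is also zero if w = 0, which is the comparison restricted to WVU.

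**Step 2: range.** Assume WVU supplies a share s of all contacts and letters supply half of the WVU contacts. Then w = (1 − s)/(1 − s + s/2).

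- s = 0.5: w = 0.50/0.75 = 0.667
- s = 0.7: w = 0.30/0.65 = 0.462

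With 100 to 300 interested volunteers, Fisher's exact test at two-sided 0.05 was simulated with 3,000 replicates per scenario and no true strategy effect:

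| Assumed yield WVU / OSU | Spurious difference, both sites together | False-positive rate, both sites together |
|---|---|---|
| 30% / 30% | 0 points | 0.03–0.05 |
| 40% / 30% | 5–7 points | 0.06–0.16 |
| 40% / 20% | 9–13 points | 0.14–0.53 |
| 50% / 20% | 14–20 points | 0.23–0.87 |

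Example: 0.667 × (0.40 − 0.20) = 0.133 and 0.462 × (0.40 − 0.20) = 0.092. Restricted to WVU, the same test rejected in 0.02–0.05 of replicates in every scenario, so it kept its level.

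**Step 3: a reversal of observed percentages.** Assume community strategies yield 40% at WVU and 20% at OSU with 60 contacts each, and letters yield 35% at WVU.

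- Both sites: (60 × 0.40 + 60 × 0.20)/120 = 36/120 = 30%, against 35% for letters, so letters look better by 5 points.
- Within WVU: 24/60 = 40%, against 35%, so letters look worse by 5 points.

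This concerns the descriptive percentages. With 20 to 200 letter contacts in steps of 20, Fisher's exact test on these figures gives p of about 0.38–0.79 over both sites and 0.52–0.79 within WVU. It is non-significant either way.

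**The case against.** The strongest reply is that the article nowhere says the data are pooled over sites or that a single test is run. It is a condensed report, and a breakdown by site is the kind of detail a full protocol or analysis plan may supply. This stands in part: a reader may infer that one pooled test has been fixed, but that is an inference from silence. What remains is that the article names a test and a model, each with strategy as the only factor, and a population covering all interested volunteers. An ordinary Fisher's exact test has no place for a stratum, so carried out as worded it ignores site.

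A reader might also infer that strategy as a whole is confounded with site. The design does not support that. Media, flyers and brochures are crossed with site, and WVU runs both letters and community methods, so the effect of letters can be separated. Contrasts among shared strategies are distorted only if their mix differs between sites.

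It is equally tempting to say that the test would rank strategies wrongly. Fisher's exact test does not rank them; only the observed percentages can reverse, as in step 3 of the working, and that example rests on assumed rates.

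Finally, the consequence is limited. The success rates are first examined descriptively, and the result is feasibility information rather than a confirmatory test. All of this is right and sets the weight of the point.

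**Conclusion.** The point holds as a minor one. As worded, the strategy comparisons leave contrasts involving letters open to any site difference in yield. The size depends wholly on quantities the article does not give: none if site yields are equal, and between 5 and 20 percentage points over the unequal yields assumed above. The location of the film classes makes a difference plausible but does not establish one. The retention, attendance, home-practice and log benchmarks in Aim 1b, the sample size and the effect-size estimates are untouched.

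**What to change.** Add a sentence or two to the recruitment paragraph of Statistical methods:

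- Compare letters with the other strategies among WVU contacts only.
- Compare the strategies shared by both sites with a site-stratified exact test.
- Add site as a covariate in the recruitment-time regression.
- Report yield by strategy within each site.

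**Cost.** The letters contrast loses the OSU contacts and so has smaller numbers and less precision. Site must be logged for every enquiry. The article does not say that it is: enquiries go to the WVU coordinator, and the screening log is described only as holding reasons for ineligibility and non-participation. If site is not yet captured, one field has to be added to the log. Nothing else in the design changes.

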**Methods:**

Forty-four adults with confirmed moderate to severe RLS will be recruited and randomized to a 12-week yoga (*n* = 22) or standardized educational film program (*N* = 22). Yoga group participants will attend two 75-min *Iyengar* yoga classes per week for the first 4 weeks, then one 75-min class per week for the remaining 8 weeks, and will complete a 30-min homework routine on non-class days. Educational film group participants will attend one 75-min class per week for 12 weeks and complete a daily RLS treatment log; classes will include information on: RLS management, including sleep hygiene practices; other sleep disorders; and complementary therapies likely to be of interest to those participating in a yoga and sleep education study.

Yoga and treatment logs will be collected weekly. Feasibility outcomes will include recruitment, enrollment, and randomization rates, retention, adherence, and program satisfaction. Program evaluation and yoga-dosing questionnaires will be collected at week 12; data on exploratory outcomes (e.g., RLS symptom severity (IRLS), sleep quality (PSQI), mood (POMS, PSS), and health-related quality of life (SF-36)) will be gathered at baseline and week 12.

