#### Randomization

Randomization will occur immediately following completion of baseline evaluations and no more than 30 days prior to initiation of the intervention. Eligible participants will be randomized using a 1:1 ratio, to the yoga (*N* = 22) or educational film group (*N* = 22), based on an allocation sequence generated by the study statistician using a randomly varying block randomization method to ensure equal distribution among treatment groups [107].

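### Two named tests do not fit their stated purpose: a one-sample runs test for baseline similarity, and Fisher's exact test for continuous adherence and fidelity data

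*Protocol article*

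**What the plan says.** Both assignments are in the protocol article under Statistical methods.

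- **Randomization success.** This is listed under feasibility of the design (A.1). It is defined as meaning that "the two groups are similar demographically and on anthropometric and exploratory outcome measures at baseline", and it "will be assessed using the one-sample run test".
- **Adherence and fidelity.** Under treatment fidelity (A.2.1), the plan names Fisher's "exact (continuous data) and chi-square tests (using benchmark cut-offs) to determine potential differences in treatment adherence and fidelity". The exact test is thus paired with continuous data, and the chi-square test with data cut at a benchmark.

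Three other places bear on the point. The Randomization section says that the list is made "using a randomly varying block randomization method to ensure equal distribution among treatment groups"; it gives no block sizes. The recruitment paragraph of Statistical methods uses Fisher's "exact test to determine whether there are any differences in recruitment rates across the different strategies", which is an ordinary categorical use. The benchmarks under Primary objective are "80% retention, 80% class attendance, 75% home practice (yoga group), and 80% completion of weekly logs serving as benchmarks for acceptability". No other section corrects either assignment.

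**The concern.** A one-sample runs test asks whether the order of a single two-valued sequence looks random. Baseline similarity is a different question: it compares the two arms on a measured variable. An analyst who follows the text could call randomization successful despite a large imbalance. If the test is applied to the allocation list, the analyst could also call a sound blocked list unsuccessful.

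Fisher's exact test works on counts in a contingency table. Given raw continuous values, it ignores both their order and their size. The planned comparison of attendance, practice or fidelity scores would then not show which arm did better, or whether either did. At stake is the reporting of one feasibility item and of the between-arm adherence and fidelity comparison.

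**Working it through.** The plan states no figure for these tests, so there is none to reproduce. The check asks what each test does when run as written.

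**Inputs.** From the protocol: 44 participants, 22 per arm, 1:1, randomly varying blocks. Assumed, because not stated: two-sided 5% level; block-size sets 2/4, 2/4/6, 4/6 and 4/6/8; true baseline differences of 0, 1 and 2 SD in a normal variable. The rejection rates in (a) and (b) come from 4,000 simulated trials per scenario.

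**1. Runs test**

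*(a) Applied to the allocation list.* With n1 = n2 = 22:

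- expected runs = 1 + 2·n1·n2/n = 1 + 968/44 = 23
- variance = 2·n1·n2·(2·n1·n2 − n)/(n²(n − 1)) = 968 × 924/(1,936 × 43) = 10.74, so SD = 3.28
- rejection needs a departure of more than 1.96 × 3.28 = 6.4 runs, that is, 16 or fewer runs, or 30 or more

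Blocking forces extra alternation, which pushes the count upward. Mean runs are from a separate simulation of 20,000 lists.

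| Assumed blocks | Mean runs | Rejects at 0 SD | at 1 SD | at 2 SD |
|---|---|---|---|---|
| 2/4 | 29.9 | 56% | 54% | 53% |
| 2/4/6 | 28.0 | 33% | 33% | 32% |
| 4/6 | 26.9 | 21% | 22% | 21% |
| 4/6/8 | 26.1 | 15% | 15% | 15% |

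An unrestricted random ordering gives 4.7%. Along each row the rate does not move, apart from simulation error, because no baseline value enters the test.

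*(b) Applied to a baseline variable, split at its median, in enrolment order.*

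| True difference between arms | Runs test rejects | Two-sample t-test rejects |
|---|---|---|
| 0 SD | 4–5% | 5% |
| 1 SD | 4–6% | about 90% |
| 2 SD | 7–15% | 100% |

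Here the false-alarm rate is correct, but the test barely responds to imbalance. The t-test is shown only as a yardstick for the size of the signal.

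**2. Fisher's exact test on continuous values**

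If all 44 values differ, the table is 2 × 44 and every column total is 1. Each possible table then has the same probability, 1/C(44,22) = 1/2,104,098,963,720 = 4.75 × 10⁻¹³. The p-value adds up all tables no more probable than the one observed. That is all of them, so p = 1 whatever the data. If every value in one arm lies above every value in the other, a rank-sum test gives p = 2/C(44,22) = 9.5 × 10⁻¹³, while Fisher's test still gives 1.

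With ties the p-value can fall below 1, but each distinct value is an unlabelled category. Relabelling the values in any order leaves the result unchanged, so it is not a test of level.

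**The case against.** **The runs test may be a misnamed two-sample version.** The Wald-Wolfowitz test, with arm labels sorted by a baseline value, does compare distributions. Under the same assumptions it has about 33% power at 1 SD and 96% at 2 SD. This may be what was meant, but the text says one-sample, and even the two-sample form is weak beside the t-test at 1 SD.

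**The 15% to 55% rates depend on one reading.** This stands. The plan does not say that the allocation list is tested, and the block sizes are assumed. A reader might infer that a sound randomization would probably be reported as failed. The documents do not support that; it is a risk on one reading only. What holds on both one-sample readings is that the test does not assess what it is assigned to assess.

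**Attendance is discrete, so Fisher's test can be run.** This also stands. Yoga has 2 × 4 + 8 = 16 classes and film has 12. The possible percentages number 17 + 13 − 5 shared = 25, so 44 people must share values and the p = 1 result need not occur for attendance. To say that the analysis is impossible would be too strong. It remains poorly matched: 15/16 can occur only in the yoga arm and 11/12 only in the film arm, and the test treats them as different categories although they are nearly equal.

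**The benchmark comparison is sound.** Agreed. A reader might infer that chi-square is wrong there because 22 × 0.2 = 4.4 participants per arm would be expected to miss a benchmark. That does not follow: an 80% cut-off for attendance or logs does not mean that 20% of people fall below it. Exact enumeration at 22 v 22 puts the size of the chi-square test at 5.15% and 5.02% for failure rates of 20% and 25%, against 2.4% for Fisher's test at both. Choosing Fisher's test there is a preference.

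**The label for continuous data may be a drafting slip.** Possibly, but nothing else in the article corrects it.

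**Conclusion.** The point holds: both assignments are wrong as written. The mismatch between test and question follows from the definitions of the tests and needs no assumption. The simulated rates rest on the assumed block sizes, level and imbalances, and the 15% to 55% range applies only if the allocation list is tested. The p = 1 result needs all values to be distinct; with ties, the fault is that order and size are ignored.

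The impact is small to moderate. Randomization success is listed under the primary feasibility aim but has no benchmark, and the fidelity comparison is secondary. A reader might infer that the feasibility conclusion or the effect sizes for the next trial are compromised. They are not, on this ground: the 80% and 75% benchmarks can be judged descriptively, and the effect sizes come from a separate ANOVA. Whether that ANOVA should adjust for baseline is a different question, which neither error raises.

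**What to change.** Change two sentences in Statistical methods.

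1. **Randomization success:** drop the runs test. Present a baseline table by arm with standardized differences for the demographic, anthropometric and exploratory outcome measures, without significance tests.
2. **Adherence and fidelity:** compare continuous or count measures between arms with a rank-sum test, or report the difference with a bootstrap confidence interval. Keep the chi-square test for data cut at the benchmarks, with Fisher's exact test where cells are sparse.

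The cost is the rewording. Design, conduct, data collection and sample size do not change.

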### Sample size

We performed a simulation study to determine the total sample size required to derive precise estimates of effect sizes for a two-arm randomized trial using a 1:1 randomization scheme for the primary intervention (yoga) and the educational film program; estimates were based on regression models using multiple simulations and scenarios, and specifically accounting for heterogeneity of effects. We considered seven combinations of effect sizes at 23 different sample sizes for total of 161 effect and sample size combinations. For each combination we ran 5000 simulations for a total of 805,500 simulations. The seven effect-size combinations were structured under the conservative assumption that all interventions would lead to a small to moderate improvement in outcomes and that the yoga intervention would lead to an improvement equal to or greater than the comparator condition. We used repeated simulations to determine the required post-attrition total sample size needed to obtain precise estimates of all three treatment effects under an intent-to-treat (ITT) analysis of variance (ANOVA) analysis. Based on findings of the simulation study and assuming 20% attrition, a sample size of 44 participants will permit reasonably precise estimates (within 95% confidence intervals of the true effect size value) for the two interventions, as well as reasonable estimates of recruitment, randomization, and adherence rates; moreover, estimates remain robust even at 30% attrition. Thus, the study will be adequately powered even if effect sizes for the yoga program are substantially smaller, and attrition rates greater than observed in our pilot studies [15, 66].

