Data on exploratory outcomes and certain modifying/confounding factors will be collected at baseline and 12 weeks to determine the effect sizes of the programs, data critical to the design of the planned larger RCT. RLS symptom severity, the primary efficacy outcome for the full-scale trial, will be evaluated using the International RLS Rating Scale (IRLS), a 10-item scale which includes questions related to frequency, intensity, and impact [89]. Considered the gold standard for measuring RLS symptoms [109, 110], this instrument is recommended for use in RLS clinical trials by the European RLS Study Group (EURLSSG) [111], and is widely used both in the US and internationally [3, 112]. Additional exploratory outcomes are sleep quality, mood, and health-related quality of life (HrQOL), endpoints recommended for inclusion in all clinical trials of RLS [26, 111]. These outcomes will be assessed via a short battery of self-report instruments commonly used in pharmaceutical trials of RLS patients [113–116]. Sleep quality will be assessed using the nine-item Pittsburgh Sleep Quality Index (PSQI) [117]; mood will be evaluated using the 65-item Profile of Mood States (POMS) [118] and 10-item Perceived Stress Scale (PSS) [119, 120]; and HrQOL will be measured using the 36-item MOS Short Form-36 (SF-36) [121, 122]. These self-report instruments are well-established scales that have been shown to be sensitive to short-term behavioral interventions, and have been validated in a wide range of populations, including RLS patients [118, 123–137]. As in our previous trials [15, 66] we will also assess potential changes in blood pressure and heart rate to determine effect sizes in these indices of sympathetic activation; heart rate and blood pressure will be measured three times at each assessment using an automated blood pressure monitor (Omron HEM-780) after a 5-min seated rest period.

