*Treatment effect sizes* (*A.2.2*), based on between-group differences in change over time, will be estimated using one-way ANOVA models. Effect size estimates will be calculated using both ITT (primary) and per-protocol analyses. These unbiased estimates of intervention effect size will inform sample size determination for our planned future efficacy trial [147]. Scores on *the Yoga-dosing Questionnaire* (*A.2.3*) will also be assessed using descriptive statistics to determine optimal scheduling and maximum acceptable dosing of yoga for our future trial.

*Missing data*: every effort will be made to minimize missing data relevant to all aims. If missing data does occur and the missing-data pattern (probability model) is not missing completely at random (MCAR), then we will consider approaches appropriate for missing at random (MAR) and missing not at random (MNAR). If the pattern or structure of the plausible missing data suggests MAR, either the EM algorithm [148], inverse weighting [149], or multiple imputation (MI) [150, 151] will be used and the missing-data mechanism will be constructed from the collected data [150, 152, 153]. The selected method will reflect the appropriateness of the method to best estimate the underlying missing-data mechanism [148–150, 152]. Participant characteristics will be assessed, including demographic and lifestyle characteristics, RLS severity, medical history, health-related factors, and baseline questionnaire scores for the estimation of plausible models (i.e., MCAR, MAR, and MNAR) for the missing-data mechanism. While we will not be able to definitively test if the missing data are MNAR, If there are indicators suggestive of MNAR (e.g., drop-outs differ significantly from non-drop-outs in key characteristics), we will use MI in conjunction with a sensitivity analysis to provide a set of plausible conclusions recognizing that each conclusion will be predicated on the assumptions necessary for constructing a MNAR missing-data mechanism model [150, 153].

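### Effect sizes are estimated by one-way ANOVA on change scores; adjusting the week-12 score for its baseline value would usually be more precise and would remove the effect of chance baseline imbalance

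*Protocol article*

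**What the plan says.** Under Statistical methods, the effect-size paragraph (aim 2.2) names its model: effect sizes, "based on between-group differences in change over time, will be estimated using one-way ANOVA models". One-way means that arm is the only term. The estimates are to be produced for an intent-to-treat and a per-protocol set, and are to inform the sample size of the planned efficacy trial.

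Each exploratory outcome has one pre and one post value: "Data on exploratory outcomes and certain modifying/confounding factors will be collected at baseline and 12 weeks to determine the effect sizes of the programs" (Data collection and outcomes). The intent-to-treat set requires a baseline assessment, so every participant in it has the covariate.

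The Sample size section bases the trial on precision under an ANOVA: "assuming 20% attrition, a sample size of 44 participants will permit reasonably precise estimates", and it adds that "estimates remain robust even at 30% attrition". Allocation is 1:1, "using a randomly varying block randomization method to ensure equal distribution among treatment groups" (Randomization). No stratification by baseline severity is stated. Baseline questionnaire scores enter the analysis text only for modelling missing data. Baseline similarity of the arms is to be checked, but no adjustment follows from the check.

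**The concern.** A change score subtracts the whole baseline value, which is the same as assuming that the week-12 score regresses on baseline with slope 1. Where the true slope is lower, subtraction over-corrects. The difference between arms is then noisier than it need be, and part of any chance baseline gap stays in the estimate with its sign reversed.

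This bears on the trial's own purpose. The number randomized is justified by the precision of the effect estimates, and those estimates feed the design of the next trial. With about 17 or 18 completers per arm, moderate chance imbalance on any one scale is not rare. The information needed to deal with it is already being collected.

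**Working it through.** **Inputs.** From the documents: 44 randomized 1:1, attrition of 20% (30% as the worse case), one baseline and one week-12 value per outcome, one-way ANOVA on change. Not given: the correlation rho between visits, the SDs, and the target interval width. Assumed here: two-sided 95% intervals, equal SDs at both visits (relaxed in step 5), and rho from 0.3 to 0.9.

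**1. The plan's figure.** 44 × 0.80 = 35.2, so about 35 completers; 44 × 0.70 = 30.8, so about 31. Conversely, 35/0.80 = 43.75, which rounds up to 44. The total is consistent with about 35 completers. The simulation behind it cannot be reproduced, because its effect combinations, SDs and precision target are not stated.

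**2. Formulas**, in units of the outcome SD, with N completers:
- Change score: Var = 2(1 - rho) × 4/N, t quantile on N - 2 df.
- ANCOVA: Var = (1 - rho²) × [1 + 1/(N - 4)] × 4/N, t quantile on N - 3 df. The bracket is the small-sample cost of estimating the slope: 1/31 = 3.2% at N = 35.
- Large-sample ratio, ANCOVA to change: (1 - rho²)/[2(1 - rho)] = (1 + rho)/2.

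**3. Numbers at rho 0.5, N = 35.**
- Change: 2 × 0.5 × 4/35 = 0.1143; SE 0.338; × 2.035 = 0.69.
- ANCOVA: 0.75 × 1.0323 × 4/35 = 0.0885; SE 0.297; × 2.037 = 0.61.
- Equivalent completers: 35 × 0.1143/0.0885 = about 45.

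| rho | half-width, change | half-width, ANCOVA | reduction | variance ratio | 35 under ANCOVA are worth |
|---|---|---|---|---|---|
| 0.3 | 0.81 | 0.67 | 18% | 0.67 | 52 |
| 0.5 | 0.69 | 0.61 | 12% | 0.77 | 45 |
| 0.7 | 0.53 | 0.50 | 6% | 0.88 | 40 |
| 0.8 | 0.435 | 0.420 | 3.5% | 0.93 | 38 |
| 0.9 | 0.308 | 0.305 | 1% | 0.98 | 36 |

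With 31 completers and rho 0.5 the half-widths are 0.735 and 0.649. The two methods break even at rho of about 0.93 for N = 35 (0.92 to 0.93 for N = 31). Above that the change score is tighter, by under 1% in half-width at rho 0.95.

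A simulation of 20,000 trials per rho (18 vs 17 completers, true effect -0.50 SD) agrees. The SD of the estimate, change vs ANCOVA, is 0.400 vs 0.329 at rho 0.3, 0.337 vs 0.298 at 0.5, 0.260 vs 0.243 at 0.7, 0.214 vs 0.206 at 0.8 and 0.152 vs 0.150 at 0.9. Both methods average -0.50 and both cover at 95%.

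**4. Chance imbalance.** With 18 vs 17 the baseline difference has SD √(1/18 + 1/17) = 0.34. A gap above 0.3 SD in either direction occurs in about 37% of trials for any one scale. The change score carries (1 - slope) times the gap into the estimate. Among simulated trials in which yoga starts more than 0.3 SD worse (mean gap 0.49), this gives:
- rho 0.5: shift 0.5 × 0.49 = 0.24, so the mean change-score estimate is -0.74.
- rho 0.7: shift 0.3 × 0.49 = 0.15, so the mean is -0.65.
- ANCOVA averages -0.50 in both.

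A gap of the same size the other way shrinks the estimate by the same amount.

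**5. Unequal SDs.** In general the slope is rho × SD(week 12)/SD(baseline), and the large-sample ratio with SD ratio k is k²(1 - rho²)/(1 + k² - 2·rho·k). Taking k = 1.3 as an assumption:
- rho 0.5: 1.2675/1.39 = 0.91, a 9% saving in variance instead of 25%.
- rho 0.7: 0.862/0.87 = 0.99, so the 3% slope cost cancels the gain.

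A ratio below 1 enlarges the gain.

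**The case against.** The strongest reply is that nothing here is wrong. A change-score ANOVA is a legitimate randomized comparison. The outcomes are exploratory, in a trial whose primary aims are feasibility and acceptability, and no test or benchmark depends on the interval width. The sample size was also worked out under an ANOVA, so sizing and analysis agree. All of this stands. It limits the point to an improvement in precision and robustness.

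A reader might infer that the estimates are biased and that the article is wrong to call them unbiased. The documents do not support that: over repeated randomizations both methods are centred on the true effect. The distortion is conditional on the imbalance that this one trial happens to have.

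A reader might also take ANCOVA to be free and always better. It is neither: it uses a degree of freedom and about 3% of variance, and its advantage depends on a correlation and an SD ratio that the documents do not give. The severity entry criterion (an IRLS item) could narrow the baseline SD, which would push the slope up and the gain down.

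That a fuller analysis plan may add covariates is possible, since the article collects modifying and confounding factors. But the article does not leave this open: it names the model.

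**Conclusion.** The point holds as a worthwhile refinement, not as an error of validity. The named model usually gives up precision that the collected data could supply, and it leaves the planning estimate exposed to chance baseline differences. With equal SDs and 35 completers, the avoidable excess is material at rho of 0.3 to 0.5, modest at 0.7, and negligible from about 0.9. A week-12 SD larger than the baseline SD reduces it further. Which of these cases applies cannot be told from the article. The consequence falls on the effect sizes carried into the design of the efficacy trial, not on the feasibility conclusions.

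**What to change.** Replace the one-way ANOVA sentence. For each exploratory outcome measured at both visits (IRLS, PSQI, POMS, PSS, SF-36, blood pressure, heart rate), model the week-12 score on arm with the same measure's baseline value as covariate. Report the adjusted difference with its 95% CI. State which SD standardizes it, bearing in mind that the entry criterion may narrow the baseline SD of the IRLS and so inflate an effect standardized by it. Change-score results may stay as a supplement.

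The cost is one reworded sentence, one degree of freedom and about 3% of variance, with no new data and no change to the number randomized.

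Do not add a site term yet. The yoga section places classes at studios for both sites, while the film section places every class at the West Virginia site, and no stratification by site is stated. As written, site may be entangled with arm. Those sections need to be reconciled first; the baseline covariate does not depend on the outcome.
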